### Treatment-as-usual

All participants will complete the essential components of the WIR treatment program. The WIR program includes daily and weekly clinical visits and both individual and group sessions. These sessions include but are not limited to cognitive behavioral therapy, cognitive processing therapy, motivational interviewing, behavioral modification and strength-based case management interventions, nutritional education, and occupational training. The WIR program is conducted in three phases, with increasing independence at each phase (e.g., supervised probation with ankle monitor and residing in program-supervised housing at first; independent housing, independent employment, and outpatient visits multiple times per week towards the end of the program). Phase 1 includes 40 structured hours weekly that is devoted to addiction and trauma treatment, parent education, job readiness training, life skills, safe group housing, education, and community volunteering. Phase 2 includes 24 structured hours weekly that is devoted to job retention training, part-time job replacement, parent-child visitation, health and wellness services, education groups, subsidized housing, financial literacy, and recovery support. Phase 3 includes 12 structured hours weekly that considered full-time employment, parent-child reunification, education groups, independent housing, recovery support technology, and community integration. Graduation from the program occurs after completion of phase 3, an average of 17 months in the program. Random drug testing is conducted by WIR throughout participation in the program. After graduation, women can continue participating in group programming on a volunteer basis. Implementing active or active-control interventions will not require alteration to treatment-as-usual.

### Interventions

#### Active control intervention

Participants in the comparison group will receive the essential components of the WIR program (TAU) plus additional WIR training sessions related to health and wellness, communication skills, and/or financial literacy, scheduled at the same days/times as the NEAT sessions. Thus, the active control intervention has the same duration and frequency as the active intervention without involving the cognitive training content designed for the active intervention.

#### Active intervention

The active intervention in this trial, the Neurocognitive Empowerment for Addiction Treatment (NEAT), was developed to target cognitive domain thoughts to be either influenced by substance use or involved in drug craving and seeking behavior based on the dynamic model of craving (DCM) (Rezapour et al. [25]). According to the DCM model (Fig. 2) which has been inspired by the traditional cognitive behavioral therapy frameworks [26], drug craving is triggered by environmental cues (E) (including both internal and external cues). These cues then elicit distinct yet collaborative bottom-up and top-down attentional processes that increase the focus of attention on drug-relevant cues (A). This attentional deployment activates saliency evaluation processes (S) related to drug-associated cues. The retrieval of memories (M) linked to the drug cues provides relevant information during saliency processing. Saliency evaluation can result in an interoceptive state that represents the subjective feeling of craving, leading to the engagement of executive control (Co) and decision-making processes to execute actions supporting drug-taking behavior or abstinence. In targeting these functions, NEAT also provides skills important for daily functioning and re-integration into the society, including self-monitoring, time management, and problem solving [27].

**Fig. 2 Fig2:**
[figure not shown]
Dynamic model of craving (DCM). A neuroscience-informed conceptual framework to define the major cognitive targets in the dynamic response to drug-related or emotionally salient cues that can end up to drug-seeking and consumption behaviors. E, environment; A, attention, S, saliency processing; M, memory; I, interoception; Co, control; R, response

NEAT consists of 14 90-min group sessions, which will be led by two trained master’s level therapists or therapists-in-training (e.g., doctoral students in clinical psychology) supervised by a licensed clinical psychologist (RLA). Groups are led by therapists according to the session-by-session manual. All sessions will be audio-recorded to support supervision and fidelity of implementation. Cartoon-based treatment binders and brain planners are provided to all participants. As the intervention is designed to be delivered in the group therapy setting during the trial and also in future clinical use, clustering of the effect due to the group administration of the intervention is not accounted as a variable of interest.

Each session starts with a didactic, psychoeducation portion describing the concepts and skills of focus in each session. The session is followed by a written material with descriptions of the concepts/skills in verbal and pictorial (cartoon) formats. The session continues with practicing cognitive tasks/games relevant for each skill and ends with a discussion of how they can monitor and practice each skill in their everyday life. Besides the in-session components, subjects are provided with homework material to practice the learned objectives between sessions, including monitoring their use of various brain functions, implementing compensatory strategies, and completing additional cognitive exercises. They are also asked to complete aspects of the brain planner between each session, starting with the retrospective recording of events and slowly progressing towards prospective planning. NEAT will target the cognitive domains shown in Fig. 3 through the use of the following five components:
Neuroscience-informed psychoeducation: The main purpose of the neuroscience-informed psychoeducation component is to promote subjects’ awareness about the cognitive impairments often associated with drug craving and addiction. Participants are provided with information concerning the common behavioral manifestations of these impairments in daily life activities. They are informed about lifestyle changes (e.g., nutrition, physical exercise, sleep) that can facilitate brain recovery. To improve learning and consolidation, the education components are accompanied by colorful and comic cartoons [28].Cognitive exercises: According to previous work, using cognitive exercises with game-like features can be useful for supporting treatment engagement and restoration of cognitive functions among people with SUDs [29]. These game-based exercises include such things as Stroop-like tasks [30], spot the differences game [31], and target cancelation tasks [32]. In NEAT, these games are used not only as a way of practicing and improving specific brain functions, but also for enhancing understanding of the brain functions discussed (e.g., as a way of demonstrating what is meant by “inhibition” or “working memory”) and supporting metacognitive awareness (the next component).Metacognitive training: Metacognition awareness [33, 34] is supported through self-monitoring in between sessions and group discussions about the cognitive functions involved in each brain exercise and the role that these functions (and the associated compensatory strategies) play in their day-to-day functioning, craving management, and substance use recovery. This component targets insight towards the cognitive foundations of the training program and aims to enhance motivation to implement skills and generalization of learning.Compensatory strategies: The main purpose of these components is to provide specific cognitive strategies for supporting optimal cognitive functioning and compensating for deficits. For example, providing mnemonic aids and goal management training for memory- and planning-related problems [35, 36]. These components are integrated with the cognitive exercises discussed above to provide a thorough understanding and awareness of the role of specific cognitive functions in their lives.Brain planner: Training participants to keep records of their daily activities, including both retrospectively (e.g., recording past events) and prospectively (e.g., planning future activities and goals), is another critical aspect of NEAT. Planner use can support optimal daily functioning and the use of higher-order cognitive functions such as self-monitoring and planning (which are also supported by compensatory strategies discussed above) but can also help compensate for deficits in these cognitive domains and others (i.e., memory deficits) [37]. The use of a planner also supports compliance with NEAT and other substance use treatment activities. Each training session of NEAT has time dedicated to learning and practicing using the planner.

**Fig. 3 Fig3:**
[figure not shown]
Architecture of Neurocognitive Empowerment for Addiction Treatment (NEAT) for 14 sessions. In each session, a new cognitive domain is added to the previous one in trainings and exercises (accumulative architecture). The brightness of color indicates the level of complexity of the cognitive modules. The basic modules (e.g., sustained attention) marked with bright colors, and the complex ones marked with dark colors (e.g., monitoring)

Based on the nature of the intervention, there are no anticipated serious adverse events (SAEs), adverse events (AEs), or harms from the intervention. In case of any minimum AEs during the assessments or intervention, the study investigators will be involved to mitigate any risks or consequences and the details will be documented and reported to the LIBR leadership team and the IRB committee (WIRB) according to the WIRB protocols. The reason for dropout for participants who discontinue or deviate from the intervention protocols will be collected for further exploratory analyses.

### Measures

Table 1 indicates the list of self-report, behavioral, and neuroimaging assessments included in the protocol (refer to Fig. 4 for the timing of assessments). We will use the total score of the Obsessive Compulsive Drug Use Scale (OCDUS) [21] as a primary outcome measure for drug craving in the past week. It is a 12-item questionnaire consisting of three factors including thoughts about drugs and interference, desire and control, and resistance against thoughts and intention to use drugs that compose a total score. The remaining questionnaires and tasks used as secondary and exploratory outcome measures are described in Fig. 4.

**Table 1 Tab1:** Diagnostic, demographic, self-report, behavioral, and neuroimaging assessments

Diagnostic and demographic assessment	
Diagnosis	MINI V6.0 [23] or the PRISM-5
History	Assessment of medication history and medication and therapy compliance
Standard self-report scales	
Substance use	Obsessive Compulsive Drug Use Scale (OCDUS) [21]
Substance use	Customary Drinking and Drug Use Record (CDDR) [38]
Substance use	Addiction Severity Index (ASI) [39]
Substance use	Desire for Drug Questionnaire (DDQ) [21]
Substance use	PROMIS Alcohol Use [40]
Substance use	PROMIS Nicotine Dependence [41]
Substance use	PROMIS Substance Use Severity [42]
Mental health	PROMIS Adaptive Scales (depression, anxiety, and anger) [43]
Mental health	Traumatic Events Questionnaire (TEQ) [44]
Mental health	Difficulties in Emotion Regulation Scale (DERS) [45]
Mental health	UPPS Impulsive Behavior Scale [46]
Mental health	Behavioral Inhibition System/Behavioral Approach Scale (BIS/BAS) [47]
Treatment engagement	Services Engagement Scale (SES) [2]
Treatment engagement	Client Evaluation of Self and Treatment (CEST) Engagement [48]
Feasibility/knowledge	Credibility/Expectancy Questionnaire (CEQ) [48]
Feasibility/knowledge	Homework Rating Scale (HRS) [49]
Feasibility/knowledge	Working Alliance Inventory (WAI) [50]
Cognitive functions (subjective)	PROMIS Cog Abilities (PROMIS-CA) [22]
Cognitive functions (subjective)	PROMIS Cog General (PROMIS-CG) [22]
Behavioral assessment	
Neuropsychological	NIH Toolbox Cognitive Assessment Battery [51]
Neuropsychological	Iowa GamblingTask [52]
Neuropsychological	Delayed Discounting [53]
Neuropsychological	Emotional and Classic Go/NoGoTasks [54]
Neuropsychological	Classic version of the go/no-go task [55]
Neuroimaging assessments	
Neuroimaging	T1-W sagittal MP-RAGE
Neuroimaging	fMRI resting state
Neuroimaging	fMRI monetary incentive delay [56]
Neuroimaging	fMRI stop signal [57]
Neuroimaging	fMRI drug cue reactivity [58]
Neuroimaging	T2-W sagittal
Neuroimaging	T2-W axial FLAIR
Neuroimaging	Diffusion tensor imaging
Laboratory assessments	
Substance use	Urine drug test
Biomarker assessment	Blood sample test

**Fig. 4 Fig4:**
[figure not shown]
Schedule of enrollment, interventions, and assessments. This figure indicates the assessments or interventions completed for screening, pre-intervention, weekly during the completion of the intervention, post-intervention, and 3- and 6-month follow-up. Participants are randomized in groups of 9–12 to complete either neuroscience-informed psychoeducation (NEAT) or active control intervention. *OCDUS*, Obsessive Compulsive Drug Use Scale; *ASI*, Addiction Severity Index; *CDDR*, Customary Drinking and Drug Use Record; *DDQ*, Desire for Drug Questionnaire; *TEQ*, Traumatic Events Questionnaire; *BIS/BAS*, Behavioral Inhibition System/Behavioral Approach Scale; *UPPS-P*, UPPS Impulsive Behavior Scale; *DERS*, Difficulties in Emotion Regulation Scale; *PROMIS*, Patient-Reported Outcomes Measurement Information System; *SES*, Services Engagement Scale; *CEST*, Client Evaluation of Self and Treatment; *HRS*, Homework Rating Scale; *WAI*, Working Alliance Inventory; *PROMIS-CA*, PROMIS Cog Abilities; *PROMIS-CG*, PROMIS Cog General

Biological specimens (blood and oral and mouth microbiome) data will be collected in the baseline for further exploratory analysis on the predictive role of biomarkers on response to interventions. Less than 150 mL of blood will be collected per subject, which is well within the safety limit of ~ 450 mL per blood draw. Blood will not be drawn from subjects with a hematocrit below 30%. A trained phlebotomist will obtain blood samples in the morning of one of the visits, or at a time convenient for the participant. Participants will also be asked to provide microbial samples during the biomarker session.

For blood samples, plasma, serum, PBMCs, and genetics will be transported to and processed at the University of Oklahoma Integrative Immunology Center (IIC) Laboratories. Plasma, serum, and genetic samples will be stored in secure freezers at − 80 °C. Freezers will be maintained in a specially equipped room with emergency backup power and an automated telephone alarm system that is programmed to call in case of failure. Additional aliquots of samples will be stored at − 80 °C should repeat analyses be required at a later date. PBMCs will be stored in liquid nitrogen dewars with liquid level monitors and alarms in a secure room at the University of Oklahoma IIC Laboratories.

Participants will also be asked to provide microbial samples during the biomarker session. All participants will be asked to provide forehead, mouth, and stool samples. A research assistant will provide the participant with an all-in-one sample collection kit system for collecting, stabilizing, transporting, and purifying samples which include cotton swabs, tubes labeled by body area, and a one-page sheet with step-by-step instructions. Once a participant has obtained all samples and provided them to the research assistant, the research assistant will label each tube with the subject’s ID number and date of sample. Once the sample has been properly labeled, it will be placed in a freezer in a locked office. The microbiome samples will be transported to the University of Oklahoma IIC Laboratory for DNA extraction and long-term storage in secure freezers at − 80 °C. Analysis of the de-identified samples will be conducted at the University of California-San Diego.

### Data management

Confidentiality will be maintained by keeping identifying information (such as names and phone numbers) in secure servers. Except for a contact form, research data will be identified by a subject number rather than by name. An alpha numeric system will be used for the identification of subjects. All hard copies of study information will be kept in locked file cabinets inside a locked office. All electronic study information will be stored on secure servers with appropriate access controls. Only study personnel will have access to the identifying data. The WIR staff will be aware of who is participating in the research study, as they will know who is attending this group versus the other WIR activities planned at that time. In addition, these treatment providers may insert into their treatment records that they attended these treatment sessions. However, treatment program staff will not be privy to any of the information provided to the research study personnel via interview, behavioral, or self-report assessments. Subject identity will not be disclosed to any person who is not authorized to see this information, except in the event of a medical emergency or if required by law. Paper copies of consents, screening forms, the research privacy form and any other forms, and testing results or papers containing personally identifiable information (PII) will be stored in locked cabinets at the Laureate Institute for Brain Research (LIBR). Any electronic data will have all identifiable information encrypted and be stored on a password-protected database on a secure server managed by LIBR.

Participants will be told that their information provided during the course of the study will remain confidential within the research study team. However, given the nature of the treatment groups held at WIR, confidentiality concerning their participation in the study cannot be guaranteed. Family members will be allowed to be present and discuss the consenting process with the participant if requested. The consent mentions the biological samples collected in this study will be stored for future research. Participants are also informed that the data collected as part of this study, including interviews and medical information, research test results, and biological specimens, may be shared with collaborators (researchers at other nonprofit research institutions, government or commercial organizations), and any data shared will not include the name or other personally identifiable information. The consent form is available from the corresponding author on request. Additionally, Certificates of Confidentiality (CoCs) will be asked from the National Institute of Health (NIH) to protect the privacy of research subjects by prohibiting disclosure of identifiable, sensitive research information to anyone not connected to the research except when the subject consents or in a few other specific situations.

### Statistical analysis

Categorical variables will be summarized by frequency and proportion, and continuous variables by mean and standard deviation (SD), or by median and inter-quartile range if the distribution, appeared skewed even after simple (e.g., log) transformations, for all participants and for participants in each treatment arm. Data normality will be evaluated by quantile-quantile (QQ) plot and Shapiro-Wilk test.

Treatment effects will be compared by the intention-to-treat (ITT) principle, i.e., all subjects who were randomized will be included in the final analysis, regardless of their adherence to any of the interventions. In order to detect changes in the variables recorded for the primary and secondary outcomes, mixed-effects model analyses will be performed using fixed-effects of time (pre-, post-intervention time points) as a within-subject factor and condition (intervention vs. control) as a between-subject factor; within-subject dependency will be captured by either random cluster and/or subject intercepts or within-subject correlation structure (e.g., 1st-order autoregressive or exponential power), whichever Akaike or Bayesian information criterion (AIC or BIC) favor. Mixed-effects models allow using all available observations and, without the need of imputation, provide unbiased estimates under the missing at random mechanism, a plausible assumption for randomized trials, and are known to be more powerful than any ad hoc imputation [59]. We include age and IQ as covariates. The inclusion of other covariates will be determined by AIC and BIC. Subgroup analyses will be conducted according to the baseline neuropsychological and fMRI characteristics. Significance level will be set at 0.05 level for the primary outcome and hypothesis; Bonferroni correction will be applied to all pre-post comparisons for all secondary outcomes, and Benjamini-Hochberg’s procedure to control false discovery rate at 5% level for all the exploratory analyses. For each outcome measure (primary, secondary, and exploratory), effect sizes of Cohen’s *d* and *f* will be computed. The effect sizes, along with the attrition rate at each time point, can be used to guide future study design.

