**Method/design:**

In a single-blind randomized controlled trial (RCT), 80 female opioid and/or methamphetamine users will be recruited from an addiction recovery program providing an alternative to incarceration for women with substance use-related offenses. Eight groups of 9–12 participants will be randomized into NEAT or treatment-as-usual (TAU). NEAT involves 14 90-min sessions, delivered twice weekly. The primary outcome is change in self-reported drug craving from before to after intervention using Obsessive Compulsive Drug Use Scale. Secondary and exploratory outcomes include additional psychological, neurocognitive, and structural and functional neuroimaging measures. Clinical measures will be performed at five time points (pre- and post-intervention, 3-, 6-, and 12-month follow-up); neuroimaging measures will be completed at pre- and post-intervention.

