Numerous cognitive rehabilitation programs have been developed to focus on compensatory strategies and restorative exercises for NCDs associated with traumatic brain injuries [17], stroke [18], multiple sclerosis [19], and schizophrenia [20]. These programs have consistently been found to improve functioning and long-term outcomes for these groups of patients. There have been a few preliminary attempts to transplant cognitive rehabilitation programs for use with substance use populations, providing initial evidence that such programs could be beneficial. However, these programs did not explicitly link the cognitive rehabilitation modules to the processes involved in addiction and recovery. There is potential value in clarifying how such strategies may relate to the current neuroscientific understanding of addiction and recovery, as well as the co-occurring symptoms often experienced.

The present pilot study aims to characterize the clinical potential for an intervention targeting NCDs in OUDs and MUDs by enhancing awareness and use of neurocognitive skills in the context of substance use recovery. This aim will be accomplished by randomizing subjects who are already enrolled in substance use treatment to complete a novel “Neurocognitive Empowerment for Addiction Treatment” (NEAT) program or treatment-as-usual intervention. NEAT is novel in (a) its use of cartoons, brain awareness games, and real-life scenarios to ensure it is interactive and engaging; (b) its focus on the role of neurocognitive deficits in recovery from substance use and co-occurring mental health symptomatology; and (c) its incorporation of neuroscience findings specific to substance use.

The primary outcome in this trial is “change in self-reported drug craving from baseline to after intervention using the Obsessive Compulsive Drug Use Scale (total score) [21]. Secondary outcome is the mean change in self-report subjective cognitive functioning from baseline to after intervention using PROMIS Cog Abilities [22] and PROMIS Cog General measures [22]. Exploratory outcomes include additional psychological, neurocognitive, and structural and functional neuroimaging measures and are available on ClinicalTrials.gov. We hypothesis that as compared to the active control, the NEAT program will be associated with the following:

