### Sample size calculation

With total enrollment of *N* = 80 and an estimated 20% attrition rate, we anticipate having complete data at our primary endpoint (post-treatment) for 32 subjects per group or 64 in total. Due to cluster randomization, the effective sample size will be *n* = (*mk*)/[1 + *ρ*(*m* − 1)] where *m*, *k*, *ρ* are the number of subjects per cluster, the number of clusters, and the intra-cluster correlation, respectively [24]; here, *k* = 4, and on average, *m*= 8 (80% of 10) per cluster. Considering a range of 0.05 to 0.3 for *ρ*, *n*_Eff_ will be somewhere between 10.3 and 23.7 per group. This effective sample size will provide a precision of *t*_*n*-1,1-*α/2*_/√*n* or 0.43–0.70, times standard deviation as margin of error at 95% confidence for a continuous measure (self-reported drug craving), and 80% power to detect large effect sizes (*d* = 0.83 to 1.3) for group differences in pre to post or pre to follow-up changes at a two-sided 5% significance of a 2-sample *t* test. While we may be underpowered to detect small to medium effects, the current pilot study will be crucial for informing the viability of the intervention and for estimating power for future, larger clinical trials.

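### The primary model uses baseline craving only as a response, so the treatment contrast is a difference in mean change; a common-baseline constraint would make the same valid model more precise

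*Protocol article*

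**What the plan says.** The abstract defines the endpoint: "The primary outcome is change in self-reported drug craving from before to after intervention using Obsessive Compulsive Drug Use Scale". The Background section repeats it as "change in self-reported drug craving from baseline to after intervention using the Obsessive Compulsive Drug Use Scale (total score").

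For the analysis, the Statistical analysis section states that "mixed-effects model analyses will be performed using fixed-effects of time (pre-, post-intervention time points) as a within-subject factor and condition" (intervention versus control) as the between-subject factor. On covariates it says "We include age and IQ as covariates", and then "The inclusion of other covariates will be determined by AIC and BIC". Baseline craving is not named as a covariate, and nothing says that the arms share a baseline mean. On missing data it says "Mixed-effects models allow using all available observations and, without the need of imputation", giving unbiased estimates under missing at random.

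The Sample size calculation section claims "80% power to detect large effect sizes", which it puts at d between 0.83 and 1.3. The test it assumes is a two-sample t test on change scores, two-sided at the 5% level. It concedes that small to medium effects may be missed.

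**The concern.** When pre and post scores are both responses and each arm has its own baseline mean, the treatment effect is the time-by-condition term. With complete data that term equals the difference between arms in mean change. A change score gives baseline a fixed coefficient of 1, whatever the pre-post correlation, so it is noisier than an analysis that estimates the coefficient.

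The two covariates that the protocol does fix cannot recover this precision. A main effect of age or IQ raises or lowers a woman's pre and post scores by the same amount, so it drops out of her change. The OCDUS baseline, already collected, is the natural covariate for later craving and is not used as one.

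Precision matters here because the trial has eight randomised groups and an effective sample of 10.3 to 23.7 per arm. Its effect sizes are also meant to guide later studies.

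**Working it through.** **Inputs.** From the protocol: 80 women in 8 groups, 4 groups per arm, 20% attrition, 32 completers per arm, m = 8 per group after attrition, intra-cluster correlation ρ from 0.05 to 0.3. Assumed: pre-post correlation r of 0.3 to 0.7, with equal variances at the two times. The protocol gives no value for r.

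**1. The plan's own figures.** n_eff = mk/[1 + ρ(m − 1)] with m = 8 and k = 4:
- ρ = 0.05: 32/1.35 = 23.7
- ρ = 0.3: 32/3.1 = 10.3

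The margins of error t/√n are 0.425 and 0.700 SD. The detectable d from the noncentral t is 0.832 and 1.301. All agree with the protocol.

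**2. Age and IQ.** In a 60-run check, adding both as main effects changed the time-by-condition estimate by 0.0 with complete data. With 20% of post scores missing, single estimates moved by at most 0.11 SD and the variance barely changed.

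**3. Complete data.** Per woman, Var(change) = 2σ²(1 − r) and Var(baseline-adjusted) = σ²(1 − r²). The ratio is (1 + r)/2, so the reduction is (1 − r)/2: 35%, 25% and 15% at r = 0.3, 0.5 and 0.7. Multiplying the plan's detectable d by √[(1 + r)/2] gives, in change-SD units and on the plan's own t-test basis:
- ρ = 0.05: 0.83 becomes 0.67, 0.72 or 0.77
- ρ = 0.3: 1.30 becomes 1.05, 1.13 or 1.20

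**4. Planned attrition.** The planned model also uses dropouts' baselines, so it does better than a complete-case change score. Per arm, in units of σ²:
- planned: (1 − r²)/32 + (1 − r)²/40
- common baseline: (1 − r²)/32

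| r | planned | common baseline | reduction |
|---|---|---|---|
| 0.3 | 0.0284 + 0.0123 = 0.0407 | 0.0284 | 30% |
| 0.5 | 0.0234 + 0.0063 = 0.0297 | 0.0234 | 21% |
| 0.7 | 0.0159 + 0.0023 = 0.0182 | 0.0159 | 12% |

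A simulation of 40,000 trials per setting, ignoring clustering and estimating the slope, gave 29%, 20% and 11%.

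**5. Clusters.** Steps 3 and 4 carry over to randomised groups only if the cluster-level pre-post correlation r_c equals the within-cluster one, r_w. In general, for group means with complete data and known variance components:
- V = ρ + (1 − ρ)/8
- C = ρ·r_c + (1 − ρ)·r_w/8
- reduction = (1 − C/V)/2

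With r_c = 0.9 (assumed):

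| ρ | V | r_w | C | reduction |
|---|---|---|---|---|
| 0.05 | 0.1688 | 0.3 | 0.0806 | 26% |
| 0.05 | 0.1688 | 0.5 | 0.1044 | 19% |
| 0.05 | 0.1688 | 0.7 | 0.1281 | 12% |
| 0.3 | 0.3875 | 0.3 | 0.2963 | 12% |
| 0.3 | 0.3875 | 0.5 | 0.3138 | 10% |
| 0.3 | 0.3875 | 0.7 | 0.3313 | 7% |

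**6. Single-slope ANCOVA of the post score.** With ρ = 0.3 and r_c = 0.9, using the within-cluster slope raises the variance above that of the change score by 34%, 16% and 1% at r_w = 0.3, 0.5 and 0.7. With a pooled slope the result runs from a 5% loss to a 4% gain.

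**The case against.** The strongest reply is that nothing here is an error. Endpoint, hypothesis, power calculation and model all target change, and the pre/post mixed model is valid under randomisation and missing at random. That stands, and the point is one of efficiency only. Chance baseline imbalance between four groups per arm is not a second harm, because it is the same loss of precision described another way.

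The second reply is that adjustment is not free with eight clusters. That stands against a single-slope ANCOVA, which can lose precision at the top of the protocol's own intra-cluster range. It would also leave out about 16 of the 80 randomised women (20%), although the plan says all will be analysed. Neither criticism reaches the common-baseline mixed model with separate cluster and subject components, which keeps every available observation and still gains 7–12% in that case. That figure treats the variance components as known, whereas in practice they come from eight groups.

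Third, age and IQ are not pointless. With dropout they can shift estimates slightly and may support the missing-at-random assumption.

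A reader might also infer two stronger faults:
- The section does not write out the interaction, so the condition coefficient could be read as averaging pre and post and giving half the effect. The stated aim of detecting changes, the hypothesis of greater reduction and the power calculation all point to the difference in change.
- Table 1 names no IQ instrument. It does list a cognitive battery, and the assessment schedule figure is not shown.

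Both are details that a condensed article may leave to the full protocol or SAP. Neither is a finding.

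**Conclusion.** The point holds as a cheap improvement to a valid analysis. As described, the primary contrast is a difference in mean change. Age and IQ contribute almost nothing to it, and baseline craving is not used for adjustment.

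The likely gain from a common-baseline model is a variance reduction of about 12–30% at the planned attrition (15–35% with complete data). This rests on an assumed r of 0.3 to 0.7 and on equal cluster-level and within-cluster correlations. If the cluster-level correlation is 0.9, the complete-data gain is 12–26% at ρ = 0.05 and 7–12% at ρ = 0.3. A flat claim of a free 15–35% gain would go beyond the document, which gives no pre-post correlation at either level.

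**What to change.** Keep the all-available-data mixed model and amend its description as follows:
- constrain the two arms to a common baseline OCDUS mean;
- name the time-by-condition term as the primary estimand;
- include cluster and subject components at each time point;
- use small-sample degrees of freedom that reflect eight randomised groups.

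Use the same form for PROMIS-CA and PROMIS-CG. Age and IQ may stay, but should not be presented as the source of precision. A single-slope ANCOVA of the post score is not the preferred form, for the reasons given above.

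The cost is analysis wording and a few extra variance parameters estimated from eight clusters. No new data are needed, since OCDUS is already measured before the intervention.
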